## Abstract

**Background:**

Most cancer patients still die in hospital, mainly in medical wards. Many studies in different countries have shown the poor quality of end-of-life care delivery in hospitals. The Program "Liverpool Care Pathway for the dying patient" (LCP), developed in the UK to transfer the hospice model of care into hospitals and other care settings, is a complex intervention to improve the quality of end-of-life care. The results from qualitative and quantitative studies suggest that the LCP Program can improve significantly the quality of end-of-life care delivery in hospitals, but no randomised trial has been conducted till now.

**Methods and design:**

This is a randomized cluster trial, stratified by regions and matched for assessment period. Pairs of eligible medical wards from different hospitals will be randomized to receive the LCP-I Program or no intervention until the end of the trial. The LCP-I Program will be implemented by a Palliative Care Unit.

The assessment of the end-points will be performed for all cancer deaths occurred in the six months after the end of the LCP-I implementation in the experimental wards and, in the same period of time, in the matched control wards. The primary end-point is the overall quality of end-of-life care provided on the ward to dying cancer patients and their families, assessed using the Global Scale of the Italian version of the Toolkit *"After-death Bereaved Family Member Interview*".

**Discussion:**

This study can be interpreted as a Phase III trial according to the Medical Research Council Framework. In this study, the effectiveness of a fully defined intervention is assessed by comparing the distribution of the endpoints in the experimental and in the control arm.

**Research ID:**

RFPS-2006-6-341619

**Trial registration:**

ClinicalTrials.gov Identifier: NCT01081899

## Background

Despite the development of palliative care services worldwide [1] and numerous studies showing that most cancer patients would prefer to die at home [2,3], most cancer patients still die in hospital [3,4]. Official Italian statistics on place of death are not available for Italy, but according to ISDOC survey [3], it is estimated that one third (34.6%) of cancer patients die in hospital, with broad geographical differences (from 60.2% in the North East to 4.6% in the South and islands). According to the ISDOC survey it is also possible to estimate that about 50% of all hospital cancer deaths occur on medical wards [3].

A number of studies carried out in different countries [5-8] have shown the poor quality of end-of-life care delivery in hospitals. Inappropriate end-of-life care may result in the continuation of invasive treatments that, in addition to having negative consequences in terms of resource management, negatively impact the quality of life of patients [9,10]. The results of two Italian studies conducted in patients who died in hospital from cancer (ISDOC) and other conditions (EOLO) confirm what observed for other countries [11,12].

Since the second half of the 90 s, research groups in the UK and the USA, have developed, implemented and started to evaluate the effect of the introduction of "Care Pathway" for end-of-life care in hospitals [13-15]. The aim of these programs was to introduce the skills necessary to address the complex needs of dying patients and their families into the hospital setting, in an attempt to transfer the "hospice expertise" into a non-specialist context.

A "Care Pathway" is a set of evidence-based, medical and care practices aimed at specific groups of patients. The Care Pathway defines the expected course of events in patient care on an established timeline. Care pathways documentation becomes an integral part of the clinical documentation and allows outcomes assessment [16]. In the healthcare setting, Care Pathways have proved to be useful in improving efficiency and effectiveness of the process of care for various pathologies [17].

Among the different Care Pathways proposed at international level, the most structured and proficient seems to be the "Liverpool Care Pathway for the dying patient" (LCP) [13]. Developed in the UK to transfer the hospice model of care into hospitals and other care settings, it is currently in use in over 20 countries [18]. The implementation of the LCP Program, after an intensive training phase, revolves around the introduction of the LCP medical chart and other specific documentation for patients who have been assessed by a multidisciplinary team to be at the end of their life. The LCP documentation provides recommendations on different aspects of care including comfort measures, anticipatory prescription of medication and the assessment of nonessential medical treatments. It also provides guidance for the psychological and spiritual support of patients and their families. The LCP documentation allows the monitoring of results and supports the implementation of audit procedures.

The Italian version of the LCP - Un percorso integrato per le cure di fine vita in ospedale (LCP-I) - has been developed by the Regional Palliative Care Network of the National Cancer Research Institute of Genoa (Italy) in compliance with the original format. The final version has been endorsed by the Central Team UK, Marie Curie Palliative Care Institute Liverpool (MCPCIL).

In Italy, the LCP-I Program has been successfully piloted in 2007 in the Medical Ward of "Villa Scassi Hospital" in Genoa. The implementation process has been evaluated using a combined qualitative and quantitative approach. Focus groups, performed on sample of doctors and nurses before and after the implementation of the LCP-I, showed a perception of effectiveness of the Program, particularly in pain management and in communication with patients and their families.

The availability of an effective quality improvement program for the care of dying patients in hospitals is particularly relevant to the healthcare scenario. The LCP-I Program has provided enough evidence to justify a randomized trial to evaluate its effectiveness. Although the core objective of the LCP-I is improving the quality of end of life care for dying patients, the Program targets the healthcare professionals working on the hospital ward. The only feasible method of assessing the effectiveness of this Program is by performing a cluster trial, where hospital wards are randomized to receive (or not to receive) the implementation of the LCP-I Program.

## Methods/Design

### Study design

This is a randomized cluster trial, stratified by regions and matched for assessment period. Pairs of eligible medical wards from different hospitals will be randomized to receive the experimental intervention (the LCP-I Program) or no intervention until the end of the trial (Figure 1). In each experimental ward, the LCP-I Program will be implemented by a Palliative Care Unit (PCU) responsible for the implementation of the Program on the ward.

**Figure 1 F1:**
[figure not shown]
**Selection and matching of pairs of wards participating to the trial**.

### Primary aim

To evaluate the effectiveness of the LCP-I Program in improving the quality of end-of-life care provided to cancer patients who die on hospital medical wards as compared to standard healthcare practices.

### Secondary aims

To evaluate the effectiveness of the LCP-I Program in terms of:

• quality of communication between the healthcare professionals, patients and families;

• quality of emotional support to family members before and after the patients' death;

• coordination of care;

• provision of care focusing on patient's individual needs;

• patient's physical well-being through a better control of physical symptoms;

• appropriateness of therapeutic and diagnostic procedures performed during the last days of the patient's life;

• quality of communication between hospital staff and General Practitioners (GPs).

### General procedures of the cluster trial

Pairs of eligible medical wards from different hospitals will be randomized to receive the experimental intervention (the LCP-I Program) or no intervention at all for the duration of the study (Figure 2). To avoid the risk of contamination, each hospital will be allowed to select only one eligible ward.

**Figure 2 F2:**
[figure not shown]
**Design of the assesment procedures**.

Immediately after randomization the PCU responsible for LCP-I implementation on the experimental ward will complete, as quickly as possible, all the organizational procedures required for the implementation of the Program. At the same time the Regional Coordination Structure will start baseline assessment in the experimental and control wards.

Baseline assessment will be performed by evaluating the quality of end-of-life care in each pair of randomized wards for all eligible cancer deaths in the 3 months before the randomization date (months -1 to -3 in Figure 2).

The LCP-I Program will be implemented in the experimental ward by the PCU (t1 to t6, Figure 2). The LCP-I Program has a duration of 6 months from the beginning of the intensive training (months 1-6 in the figure). No intervention will be implemented in the control ward until the end of the evaluation.

Effectiveness assessment (t7 to t12, Figure 2) will be performed by evaluating the quality of end-of-life care in each pair of randomized wards for all eligible cancer deaths occurring in the six months after the conclusion of the LCP-I Program in the experimental ward (months 7 to 12 in Figure 2).

### End-points

Primary and secondary end-points will be evaluated using the same procedure for all eligible cancer deaths, in the baseline and in the effectiveness assessment.

The primary end-point of this trial is the overall quality of end-of-life care provided on the ward to dying cancer patients and their families. The quality of end-of-life care will be assessed using the Global Scale of the Italian version of the Toolkit *"After-death Bereaved Family Member Interview*" [19,20]. The Toolkit is a semi-structured interview with the nonprofessional caregiver closest to the dying patient during the last days of life in hospital. The interview is focused on the patient's last week of life (or less for patients with shorter hospital stays) and on care provided to the caregivers before and after the patients' death.

The secondary aims will be assessed through an analysis of:

1. other six scales from the Toolkit *"After-death Bereaved Family Member Interview"*.

a. Informing and promoting shared decision-making

b. Encouraging advance care planning

c. Focus on individual

d. Attending to the emotional and spiritual needs of the family

e. Providing coordination of care

f. Supporting the self-efficacy of the family

2. Symptom scales from the Italian version of VOICES [21]

a. Pain

b. Breathlessness

c. Nausea and vomiting

3. Diagnostic and therapeutic procedures effectively performed during the last 3 days of life

4. The outcome of an interview with the GPs of patients who died on the wards and who are eligible for the assessment

Furthermore, the evaluation of two leaflets included in the LCP-I Program and delivered to family members after the patient's death is foreseen:

a. "Some useful information", a leaflet delivered to the family members immediately after patient's death.

b. "Facing the loss" a leaflet delivered to bereaved family members during a meeting after the patient's death.

The evaluation of the two leaflets is limited to the families of patients hospitalized in the experimental wards.

### Eligibility criteria

#### Ward level

The inclusion criteria for each medical ward are:

• classified in the regional records as "Medical", "General Medical" or "Internal Medical";

• at least 25 cancer deaths on the ward per year. The data can be estimated from a review of deaths occurring on the ward over a minimum 6 month period during the two years preceding the start of the trial

• consent from the Hospital Management to participate to the trial

• consent from the Head of the Medical Ward to participate to the trial

• consent from an expert and skills-trained PCU to implement the LCP-I Program

Exclusion criteria:

• if in the same hospital another Medical Ward has already been randomly selected to participate in the research program (regardless of which arm was randomized).

#### Individual level

For the two assessment periods (baseline and effectiveness assessment) all cancer patients deceased in the ward during the evaluation period will be considered eligible. ICD- IX criteria will be used to identify cases from the original death certificate. If the patient was a relative of a doctor or a nurse working in the hospital where the ward is located the patient will be considered ineligible.

### Procedures of assessment (Figure 3)

**Figure 3 F3:**
[figure not shown]
**Procedures of assesment for the eligible population**.

Primary and secondary end-points will be evaluated for all eligible cancer deaths as follows:

**1. Identification of eligible cancer deaths from the ward: **the cancer deaths in the ward will be identified through the hospital's deaths documentation (which lists all deaths regardless of cause). Cancer deaths will be identified by the International Classification of Diseases-Ninth Revision (ICD-IX) criteria, applied to the causes of death as reported in the death certificate of the Italian National Institute of Statistics (ISTAT).

**2. Access to medical and nursing documentation **for the assessment of care procedure

3. Assessment of care procedures

**4. GP identification: **name, address and telephone number of the GPs will be obtained by medical documentation. However, all information are available in the Regional Health records.

**5. Caregiver identification: **information regarding the patients' principal caregiver (name, relationship, address and telephone number), as reported in the medical documentation, must be acquired. The principal caregiver is the person who was closest to the patient during his/her last week of life in hospital. It can be a family member (most frequent) or a friend. If the patient had no caregiver, the interview cannot be performed and the circumstances should be described in detail.

**6. Letter to GPs: **an official letter, signed by the Regional Coordinator, describing the survey and announcing the telephone interview is sent to the deceased' GPs.

**7. GPs telephone Interview: **this must take place within 4 months of the patients death and focuses on two aspects:

◦ communication between ward staff and GPs

◦ confirmation or integration of information regarding the patient's caregiver (name, relationship, address and telephone number).

**8. Final Caregiver identification: **obtained from two main sources: medical documentation and/or patients' GPs.

**9. Caregiver Letter: **an official letter, signed by the Regional Coordinator, introducing the study and announcing the telephone interview is sent to the caregiver.

**10. Phone contact with caregiver: **it occurs 4-5 days after the letter is sent out. The interviewer refers to the contents of the letter and invites the caregiver to participate in an interview at a location of their choice.

**11. Caregiver Interview: **the Caregiver Interview must take place between 2 and 4 months after the patients' death. it should be a face to face interview in a location chosen by the caregiver. Only in exceptional cases where the caregiver is unable to attend the face to face interview (i.e. the caregiver lives in inaccessible location) then the interview may be conducted by phone. When the caregiver is obviously distressed and unable to complete the interview, priority should be given to the section of the Toolkit relative to the overall evaluation (the 6 summary questions).

### Randomisation

Randomization is centralized at the Trial Center of the National Cancer Research Institute (IST) of Genoa. The Regional Coordinators contact the IST Center for the randomization of coupled wards. Randomization lists for each region participating in the trial will be compiled by the Trial Center. The randomization will be carried out for pairs of wards. The sequence of each list will be defined by blocked 1:1 allocation. The randomization of the wards will be conducted by the Regional Coordinators by telephone or fax.

For each request, the trial center:

• verifies the eligibility of the coupled wards

• assigns a numerical code to the two wards

• records the allocation of the wards

## The LCP-I Program

The LCP-I Program is a continuous quality Improvement Program of end-of-life care implemented by a Palliative Care Unit (PCU) in a hospital Medical Ward. The Program is articulated in 10 steps.

### Step 1-3: Development of the implementation project on the ward

• **Step 1: Establishing the project - preparing the environment**

◦ Identify and describe the characteristics of the ward

◦ Identify and describe the characteristics of the PCU

◦ Obtain consent from the subjects involved

◦ Present the general outlines of the LCP-I Program to the ward staff

◦ Outline the LCP-I Program on the ward

◦ Begin the approval procedure for the training program

◦ Register the Project at the National Center for LCP-I

• **Step 2: Developing the Documentation**

◦ Acquire educational materials for training

◦ Prepare the necessary documentation for the ward

• **Step 3: Base review - Retrospective evaluation of variances related to end of life care on the ward**

◦ Review the medical documentation of the patients who died on the ward

◦ Investigate the variances with the ward staff

### Step 4-8: Implementation of the Program on the ward

The implementation of the LCP-I Program, following an intensive training phase, revolves around the introduction of the LCP-I medical chart and other specific documentation for patients who have been assessed by a multi-professional team to be approaching the end of their life. The LCP-I documentation provides recommendations on different aspects of care including comfort measures, anticipatory prescription of medication and the assessment of not appropriate medical and nursing interventions. It also provides guidance for the psychological and spiritual support of patients and their families. The LCP-I documentation allows the monitoring of results and supports the implementation of audit procedures.

• **Step 4: Induction of the Program. Intensive Education Program (duration less than a month)**

◦ 3 modules of 4 hours (12 hours total) repeated twice to allow the participation of all clinical ward staff (doctors and nurses).

• **Step 5: Clinical implementation of the LCP-I documentation. Intensive support to the ward staff (6 weeks)**

◦ the ward staff, closely supported (coaching, telephone and direct guidance, discussion of clinical cases) by the PCU team overseeing the implementation process, starts using the LCP-I documentation for dying patients.

• **Step 6: Semi-intensive support to the ward staff (6 weeks)**

◦ the ward staff, accompanied by the PCU team overseeing the implementation process, learns to use the LCP-I documentation as standard procedure for dying patients. Clinical audits are planned for difficult cases.

• **Step 7: Evaluation and further Training (end of the 4° month)**

◦ the PCU team evaluates the outcome of the preliminary steps with the aim of developing an appropriate training strategy for the ward staff during the subsequent stages of the implementation process.

• **Step 8: Consolidation phase (2 months)**

◦ the LCP-I documentation is established in the ward as an indicator of the quality of end of life care for all dying patients. The PCU team supports the ward staff using the most suitable tools for consolidation of the changes introduced by the LCP-I Program.

### Step 9-10: sustainability of high standards of quality of end of life care on the ward

If the ward staff evaluates positively the use of the LCP-I documentation for dying patients, the PCU responsible for the implementation process, actively supports the development of a sustainable policy for the ward and hospital management. The strategy revolves around the institutionalization of the LCP-I documentation. A feasible approach is the development of a care strategy that guarantees and documents the maintenance of high standards in the quality of end of life care provided.

• **Step 9: Initiation of a strategy for sustainability**

◦ the LCP-I is established as routine procedure on the ward and in the hospital

◦ develop an end-of-life care strategy for the ward.

• **Step 10: Regional and national strategy**

◦ use the outcome of the trial study to stimulate discussions at a regional and national level regarding issues linked to the quality of end-of-life care

### Statistical methods

#### Primary end-point

The primary end-point of this trial is the overall quality of the end-of-life care provided by the ward staff to dying cancer patients and their families. The quality of end-of-life care will be assessed using the Global Scale of the "*Toolkit After-death Bereaved Family Member Interview*".

The Global Scale of the Toolkit is a combination of 6 items that are evaluated at the end of the interview on a 0-10 scale (see page 15 of the Toolkit). The scores of the 6 items are added up and linearized on a 0-100 scale where 0 equals poor quality and 100 equals high quality of care. Where answers are missing for one or more of the 6 items, the score is estimated for the item for which valid answers are available. To calculate the score on the Global Scale a minimum of 4 valid answers out of 6 are necessary.

The quality of the end-of-life care provided to dying patients, assessed with the Global Scale of the Toolkit, is expressed on a 0-100 scale where 0 equals poor quality and 100 equals excellent quality of care.

#### Sample size

An absolute increase of average scores on the Global Scale of the Toolkit of 10-15 points (in experimental wards compared to control wards) can be considered the minimum difference of clinical interest which justifies the implementation of the LCP -I Program. This increase, based on the results of the pilot study corresponds to an Effect Size (ES) of about 0.4. In order to estimate sample size in a cluster trial, along with Type I and II errors, two elements are essential: the intra-cluster correlation coefficient and the average size of the cluster (number of cluster deaths) [22]. So, for this trial:

◦ the intraclass correlation coefficient can be estimated between 0.01 and 0.05 [23]

◦ according to the review of cancer deaths on the Medical Wards potentially involved, we can expect an average number of cancer deaths in the 6 months of the assessment ranging between 15 and 20.

◦ it is foreseen that the regions participating will be able to randomize 10 pairs of Medical Wards (20 clusters overall).

Data in the Table 1 intersect three ICC scenarios (from 0.01 to 0.1) with 4 scenarios of average cluster size (from 10 to 25). In the corresponding sections the total cluster required to achieve a cluster trial with a coefficient of 80% are reported to a two-tailed alpha error of 0.5 and an a hypothetical ES of 0.4. Table 1 reports different sample size scenarios necessary to detect an ES of 0.4 with alpha = 0.05 and a power of 80% conditional to the hypothesized levels of ICC (from 0.01 to 0.10) and average size of the clusters (from 10 to 25). According to the information reported in the previous paragraphs, it seems realistic to assume that the study is feasible with a total number of clusters no greater than 20 [22].

**Table 1 T1:** Total number of clusters required according to different cluster sizes and ICC (ES = 0.4, alpha = 0.05, power = 0.80).

	Average size of the clusters			
	
Intraclass Correlation Coefficient	10	15	20	25
0.01	22	**16**	**12**	**10**
0.05	30	24	**20**	**18**
0.10	38	32	30	28

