1. collection and elaboration of data in the patients' medical documentation

2. contact and interview with the caregivers

Regarding collection and elaboration of data from patients' medical documentation:

• the processing of data included in medical documentation is considered of significant public interest, to that purpose, in agreement with Articles 20 and 21 of the Italian Confidentiality Laws, it is accessible to the National Health Service and other Public Health organizations for the planning, management, monitoring and evaluation of healthcare;

• in theory the evaluation could be subject to informed consent of the terminal cancer patients (patients who might die of cancer). In fact, the patients involved in the Program evaluation, who are nearly always incapable of giving valid consent, are identified after death (as cancer deaths), regardless of whether they were hospitalized in a ward where it LCP-I Program was implemented;

• in all cases, where the patients are competent and aware of their health status (parameters previously assessed independently in the LCP-I Program) and where there is considered no risk to the patient, the clinical ward staff will be trained to deliver information to the patient and to ask them the consent to the use of personal data. This procedure will be recorded in the medical records;

• during the study and in subsequent publications, any personal data will be disaggregated and made anonymous.

Regarding contact with the caregivers, the initial contact will be made through a personal letter which includes detailed information and requests their permission to be contacted by telephone. The caregiver will be contacted by phone after at least 3 days and will be invited to participate in the interview. The interview will be conducted by specifically trained staff.

This procedure has been used successfully in the ISDOC survey [21], with very satisfactory results:

• sampling of 2,000 cancer deaths in 30 Italian Local Healthcare Authorities' areas.

• caregiver identification in 95% of cases (N = 1900)

• realization of 1271 valid interviews (64% of the sample).

• reasons for non-completion of the interviews: no caregiver identified (5%), refusal (20%), caregiver not contactable (8%), other (3%).

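### Sample size counts cancer deaths as the cluster size, although the primary endpoint exists only for completed caregiver interviews; at the 64% completion of the cited precedent, 20 wards fall below 80% power over most of the planned range

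*Protocol article*

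**What the plan says.** In the protocol article, Sample size, the average cluster size is defined as a number of deaths, and the planning value is given in the same unit: "we can expect an average number of cancer deaths in the 6 months of the assessment ranging between 15 and 20". The target difference "corresponds to an Effect Size (ES) of about 0.4", and "the intraclass correlation coefficient can be estimated between 0.01 and 0.05". Ten pairs of wards, 20 in all, are expected. Table 1 lists the total clusters "necessary to detect an ES of 0.4 with alpha = 0.05 and a power of 80" per cent, for average sizes 10 to 25. From it the section concludes that "it seems realistic to assume that the study is feasible with a total number of clusters no greater than 20".

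Other sections show what an observation of the primary endpoint requires. Under End-points, the Global Scale comes from an interview with the closest non-professional caregiver. Under Procedures of assessment, no interview is possible if the patient had no caregiver. Under Primary end-point, at least 4 of the 6 items must be answered. Under Ethical issues, the protocol says that the caregiver-contact procedure was already used in the ISDOC survey of 2,000 cancer deaths, with the result "realization of 1271 valid interviews (64% of the sample"). The losses are itemised there as 5% with no caregiver, 20% refusals, 8% not contactable and 3% other.

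**The concern.** A death is not an observation of the primary endpoint; a completed interview is. The protocol holds a completion figure for its own procedure in one section and sizes the trial in another as if every death would yield a score. The number of wards rests on that calculation. If the analysable cluster is smaller than the one entered in Table 1, the power of 20 wards is overstated, and a reader of a non-significant result would credit the trial with more ability to detect the target difference than it had.

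**Working it through.** **Inputs.** Effect size 0.4, two-sided alpha 0.05, power 80%, ICC 0.01-0.05, 15-20 deaths per ward and 20 wards (10 per arm), all from Sample size. One sentence there prints "two-tailed alpha error of 0.5"; the table title and the reproduction below show that 0.05 was used. Completion is 1271/2000 = 63.6%, reported as 64%, from Ethical issues (5 + 20 + 8 + 3 = 36% lost).

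**Reproducing Table 1.** Individuals per arm without clustering: n = 2(1.960 + 0.8416)²/0.4² = 98.1. Design effect: DE = 1 + (m − 1)·ICC. Wards per arm = n·DE/m, rounded up, then doubled.
- m = 15, ICC 0.01: 98.1 × 1.14/15 = 7.46, so 16 wards.
- m = 20, ICC 0.01: 98.1 × 1.19/20 = 5.84, so 12.
- m = 15, ICC 0.05: 98.1 × 1.70/15 = 11.12, so 24.
- m = 20, ICC 0.05: 98.1 × 1.95/20 = 9.57, so 20.

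All 12 cells reproduce exactly, so no allowance for missing interviews is hidden in the table.

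**Entering interviews instead of deaths.** At 64%, m = 15 × 0.64 = 9.6 and 20 × 0.64 = 12.8. Power of 20 wards = Φ(0.4·√(n_eff/2) − 1.960), with n_eff = 10m/DE per arm.

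| Deaths | ICC | DE at 64% | n_eff per arm | Power, no loss | Power at 64% | Wards needed, no loss | Wards needed at 64% |
|---|---|---|---|---|---|---|---|
| 15 | 0.01 | 1.086 | 88.4 | 90.1% | 75.8% | 16 | 24 |
| 20 | 0.01 | 1.118 | 114.5 | 95.6% | 85.7% | 12 | 18 |
| 15 | 0.05 | 1.430 | 67.1 | 75.7% | 64.0% | 24 | 30 |
| 20 | 0.05 | 1.590 | 80.5 | 81.7% | 71.8% | 20 | 26 |

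**Where 20 wards still suffice at 64%.** 17.5 deaths at ICC 0.01 gives 81.4%, 20 deaths at ICC 0.01 gives 85.7%, and 20 deaths at ICC 0.02 gives 82.1%. On an even grid over 15-20 deaths and ICC 0.01-0.05, about 87% of scenarios fall below 80% power, against about 9% with no loss.

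**Detectable effect size at 80% power with 20 wards, ICC 0.05, 64% completion:** (1.960 + 0.8416)·√(2/n_eff) = 2.8016 × √(2/67.1) = 0.48 for 15 deaths, and 2.8016 × √(2/80.5) = 0.44 for 20 deaths.

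**Sensitivity to the completion rate.** At an assumed 80%, m = 12-16. Power is 83.7% and 91.6% at ICC 0.01 (15 and 20 deaths), and 70.2% and 77.2% at ICC 0.05.

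**Sensitivity to the method.** The normal approximation is the lenient choice. With a t reference on 18 df, the four corners at 64% are 71.1%, 81.6%, 59.2% and 67.0%, in the table's order.

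**The case against.** The strongest reply is that 64% is borrowed. It comes from a survey sampling deaths across Local Healthcare Authority areas, not from medical wards. This trial finds caregivers through ward records and GPs, and gives priority to the six summary questions when a caregiver is too distressed to finish. Completion could be higher. That stands, and it is why 64% should be shown as one scenario in a range. It does not remove the point: it is the only completion figure in the document, it is cited in support of this procedure, and at 80% completion power at ICC 0.05 is still 70-77%.

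A second reply is that Statistical analysis adjusts for baseline quality of care, which the calculation ignores. Suppose ward effects are perfectly stable and the 3-month baseline yields half as many interviews. The variance of a ward mean then falls from v₁ = ICC + (1 − ICC)/m to v₁ − ICC²/v₀, with v₀ = ICC + (1 − ICC)/(m/2). At ICC 0.05 and 64% completion this is 0.149 to 0.139 (15 deaths) and 0.124 to 0.112 (20 deaths), and power rises only to about 67% and 76%.

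Third, Table 1 already has a size-10 column, close to 9.6, showing 22 and 30 wards, and the conclusion is worded cautiously. True, but nothing connects that column with interviews, and the text directs the reader to 15-20.

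Several stronger readings are tempting and not supported:
- That 20 wards simply fail to give 80% power. They still give 81-86% in the low-ICC scenarios listed above.
- That the whole shortfall at 15 deaths and ICC 0.05 comes from non-response. Table 1 already asks for 24 wards there, and 20 wards give 76% with every death interviewed; the loss takes it from 76% to 64%.
- That Table 1 is miscalculated. It is not; the fault lies in what is entered as cluster size.
- That the entry threshold of "at least 25 cancer deaths on the ward per year" sets the relevant size. Such a ward would give about 12.5 × 0.64 = 8 interviews, but the table works with the average ward.

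**Conclusion.** The point holds in conditional form. The section uses the wrong unit for cluster size and makes no allowance for interviews that are not obtained. If the precedent's 64% applies, 20 wards give about 64-86% power over the plan's own range, against 76-96% with no loss, and power is below 80% over most of that range. Two of the three bolded cells within the range no longer fit within 20 wards: 15 deaths at ICC 0.01 goes from 16 to 24, and 20 deaths at ICC 0.05 from 20 to 26. The third, 20 deaths at ICC 0.01, goes from 12 to 18 and still fits. These figures rest on the plan's own formula, effect size and ICC range, on 64% as an assumed completion rate, and on no credit for baseline adjustment.

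**What to change.** In Sample size:
- Define average cluster size as completed caregiver interviews.
- Re-enter Table 1 with deaths multiplied by an assumed completion rate: 64% as the precedent, with a range such as 64-80%.
- Restate the power of 20 wards for an effect size of 0.4: about 76-86% at ICC 0.01 and 64-72% at ICC 0.05 with 64% completion; 84-92% and 70-77% with 80%.
- Give the effect size detectable at 80% power (0.44-0.48 at ICC 0.05 and 64% completion).
- State that the baseline adjustment is not in the calculation.
- Keep the statement that no more than 20 clusters are needed only for the scenarios where it holds.

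The cost is rewording, a recomputed table and a less favourable stated power. The fix requires no extra wards and changes neither the design nor the analysis.
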